### Secondary hypotheses

Nursing practice outcomes: An optimal fidelity of nurses to the recommendations within the CPG for insertion and management of peripheral venous catheter in hospital wards receiving the intervention will translate into reduced care variability, increased documentation about PVC use in nursing records and greater requests of catheter tip culture from PVCs removed from patients experiencing adverse events.Clinical outcomes: The fidelity of nurses to the recommendations within the CPG for insertion and management of peripheral venous catheter in hospital wards receiving the intervention will reduce unnecessary PVCs and decrease hospital length of stay (HLOS).Health economic outcomes: The implementation and development costs of the intervention will be offset by savings from decreased incidence of CRBSIs and HLOS.EBCP environment: The contextual and individual factors on the utilization of knowledge in clinical practice decisions and impact on hospital ward processes and practice measured by Nursing Work Index (NWI) [29] and Evidence-Based Practice Questionnaire (EBPQ) [30].

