### Secondary outcome measures: process evaluation

Nurses’ adherence to CPGs will be measured at 3, 6, 9, and 12 months with the following subcategories:1.1Multimodal intervention content will be delivered as planned (yes/no), and dosage will be delivered as often and long as planned (yes/no); face-to-face training session will be assessed by measuring the number of nurses who completed the Masterclass at the intervention phase. Feedback will be evaluated by checking the distribution of clinical audit results within intervention wards. Patient information will be assessed by monitoring the presence of informative leaflets on the ward (yes/no) and asking if the patient is aware of use of PVC and prevention recommendations for personal care. Facilitation will be measured by number of internal facilitators who completed the intervention.Clinical audits on use of PVC. Device utilization ratios will be measured by percentage of PVCs per hospital wards and number of PVC per patient. Documentation of PVC in nursing records will be assessed by percentage of fully completed records. PVC maintenance will be monitored by random, monthly clinical audits, which will document PVC size (16/18/20/22/24 gauge), site (dorsum of hand/forearm/antecubital region/upper arm), dressing integrity (clean/dry/intact), securement and time in situ (less 48 h/ between 48 and 96 h/more 96 h). Catheter tip will be measured by number of catheter tip extraction following removal of PVCs.Routine practice. Clinical effectiveness questionnaire for the prevention of PVC complications will be completed pre and post intervention. The questionnaire is made up of 35 questions in four sections, relating to general asepsis and skin antisepsis; PVC insertion, maintenance, and removal; PVC documentation; and patient and professional education.Clinical outcomes will be assessed using rates of unnecessary PVCs, rates of CRBSI, extravasation, obstruction and phlebitis, defined as per standard guidelines, and mean HLOS associated to PVC-BSIs at 3, 6, 9, and 12 months.The direct costs of implementing the multimodal intervention will be assessed using HLOS for patients and decrease rates of adverse events at 12 months (post intervention).EBCP environment:EBCP context: The contextual factors on the utilization of knowledge in clinical practice decisions and impact on hospital ward processes and practice will be assessed using the NWI tool pre-intervention. The variables are summarized into five main groups: nurses’ participation in hospital affairs; quality of nursing care; nurse management’s capacity, leadership, and support for nursing staff; size of the nursing workforce and adaptation of available human resources, and professional relation between doctors and nurses.EBCP individual: The opinions, attitudes, abilities and motivations of nurses and their links with the development of a culture of clinical practice based on the transfer of new knowledge to the healthcare given to patients will be assessed using EBPQ pre-intervention. The questionnaire is made up of 24 questions relating to professionals’ knowledge, use and attitudes towards EBCP.

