
### Sample size

Calculations are based on a previous observational pilot conducted in Manacor Hospital, which reported a global rate of 44.1% PVC-associated adverse events (16% phlebitis, 6.8% obstruction, 18.1% extravasation, and 3.2% CRBSIs rates of which 3.1% were CRBSIs type 1, 0.14% CRBSIs type 2, and none CRBSIs type 3). Similar studies have a potential for improvement between 7 and 19% in adverse event rates, such as phlebitis, infiltration, and obstruction, yet there is no statistical significance or potential for improvement in CRBSI rates [32, 33]. The initial assumption is for the intervention to decrease the rate of adverse events associated with PVC in the intervention group at 6 months post-intervention by 15%. For such target result, the sample size required would be 1920 nursing records, accepting an alpha risk of 0.05, a beta risk of 0.2 in a two-sided test, and 10% missing data. For the calculation of sample size, the smallest detectable difference with adequate power and statistical significance has been considered. The sample size has been corrected to account for within-intra cluster correlation coefficient of 0.01 to allow for a design effect of 1.99. The final sample size will therefore be of 3821 nursing records, assuming an average cluster size of 200 nursing records.

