### Data collection

To mitigate control bias, each nurse manager will be provided with information to standardize catheter removal, catheter tip culture, and hemoculture extraction. Tips from all PVC removed from patients experiencing adverse events will be cultured using a semiquantitative method. Clinical, microbiological, and ward information will be collected from each patient on PVC removal.

Project investigators will collect primary and secondary outcome data using a wide range of methods, including questionnaires NWI and EBPQ to nurses, clinical audits monthly, and clinical outcome by requesting statistics report the participating wards at each hospital with the variables. Where these data are not available, clinical outcome data will be adapted from our research to collect the primary and secondary outcome data. Tools will be used for communication between facilitators, auditors, and researchers to collect at the time of activity and throughout the duration of the intervention. The mean hospital length of stay for relevant wards will be collected as reported by the hospital electronic patient management systems. This data collection system was piloted in five of the above hospital units in December 2017. Adverse events will be defined as per international guidelines for the prevention of BSIs (Healthcare Infection Control Practices Advisory Committee, USA, UK, Spain) [46–48]. Three study phases will be planned for the PREBACP study: baseline (2 months), intervention and evaluation (12 months) (Fig. 2).

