### Data analysis

#### Effect evaluation and process evaluation

Quantitative methods will be used to analyze nursing practices, health service utilization, and economic outcomes. Main and secondary outcome analyses will be based on all randomized wards and selected participants. To account for within-patient correlation, due to multiple measurements from the same patient during assessment days, we will implement generalized estimating equation models with binary outcome and logic link for all rate outcome comparisons. The statistical analysis will consist of an exploration of the descriptive data of the sample, bivariate analysis with parametric and non-parametric tests, depending on the nature of the distributions (correlation, ANOVA, chi-square) and multivariate (multiple regression with independence analysis using Durbin-Watson statistics). The Cochran-Mantel-Haenszel test will be used to compare proportions. A series of exploratory analyses will be conducted on sub-groups and the impact of covariates on estimated of the effects of the intervention. A nonparametric median test will be used for HLOS comparison. In supportive analysis, HLOS will be considered as time to event data. Survival rates will be calculated and illustrated by the Kaplan-Meier method and further analyzed by the long rank test for univariate analysis. Variables that reveal prognostic or effect modifying potential on the outcome as suggested by univariate analysis will subsequently be evaluated by the proportional Cox regression for multivariate analysis. Hazard ratios with corresponding 95% confidence intervals will be reported. A *p* value of < 0.05 will be considered statistically significant. A regression model will be constructed to further explore the results obtained in the bivariate analysis, seeking to establish an explanatory model on the variables involved in improving the use of recommendations. Data will be analyzed using the program SPSS [name] Statistics version 21.

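### Length of stay has no single population, summary or data level: the listed outcome is a mean in a handful of PVC-BSI cases, and the ward means to be collected cannot support the planned survival analyses

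*Protocol article*

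**What the plan says.** The protocol article deals with hospital length of stay (HLOS) in four sections.

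- **Secondary hypotheses.** Guideline fidelity on wards receiving the intervention "will reduce unnecessary PVCs and decrease hospital length of stay (HLOS"; nothing restricts this to infected patients. The economic hypothesis also counts on savings from shorter stay.
- **Secondary outcome measures: process evaluation.** The clinical outcome is "mean HLOS associated to PVC-BSIs at 3, 6, 9, and 12 months". The cost outcome in the same section uses "HLOS for patients and decrease rates of adverse events at 12 months".
- **Data collection.** "The mean hospital length of stay for relevant wards will be collected as reported by the hospital electronic patient management systems". Separately, "Clinical, microbiological, and ward information will be collected from each patient on PVC removal", but stay is not named among these items.
- **Effect evaluation and process evaluation.** "A nonparametric median test will be used for HLOS comparison". Then: "In supportive analysis, HLOS will be considered as time to event data", with Kaplan-Meier curves, a log-rank test and Cox regression.

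Two other sections bear on the reading. Definitions uses the term PVC-BSI for CRBSI type 3, the form confirmed by blood culture. Sample size reports the pilot as "3.2% CRBSIs rates of which 3.1% were CRBSIs type 1, 0.14% CRBSIs type 2, and none CRBSIs type 3".

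**The concern.** These are explicit statements that disagree, so a fuller analysis plan could not simply add detail to them; some would have to change. They differ on who is measured (all patients on the ward, or PVC-BSI cases), on the summary (mean or median) and on the data level (one figure per ward, or one stay per patient).

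Two consequences follow if the text is applied as written. First, the listed outcome is confined to patients who develop an infection after randomisation that the intervention is meant to prevent. The arms are then no longer compared as randomised. Any saving in bed days from an infection that was prevented also drops out of view, because that patient is not in the group. Second, an extract of ward means cannot supply the survival analyses.

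HLOS is a named secondary hypothesis, and the economic hypothesis leans on it. Without one definition, population, summary and data level could be chosen after the results are known.

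**Working it through.** **Inputs from the article**
- PVC-BSI incidence: 0.1 to 0.5 per 1000 catheter days (Background).
- Planned records: 3821 (Sample size). This reproduces from the article's own steps: 1920 × 1.99 = 3820.8, rounded up to 3821. No sample size is stated for HLOS, so 3821 serves here only as an exposure base.
- Pilot rates: 3.2% for all CRBSI, 3.1% type 1, 0.14% type 2, none type 3 (Sample size).
- 20 wards allocated 1:1 (Setting; Randomization), so about 10 per arm.

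**Assumptions, not in the article**
- One catheter per record and a mean dwell of 2 to 5 days.
- For the figures per time point, 3821 is the trial total, spread evenly over two arms and four time points.

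**Reading 1: PVC-BSI cases only, as in the outcome list**

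Expected cases = records × dwell × incidence / 1000.
- Low end: 3821 × 2 = 7642 catheter days; 7642 × 0.1 / 1000 = 0.76 cases.
- High end: 3821 × 5 = 19,105 catheter days; 19,105 × 0.5 / 1000 = 9.55 cases.
- Per arm and time point, dividing by 2 × 4 = 8: 0.10 to 1.19 cases.
- Chance that an arm has no case at a given time point (Poisson): exp(−0.0955) = 91% at the low end and exp(−1.19) = 30% at the high end.

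At the pilot's rates:
- Type 3: 0 cases.
- Type 2: 0.0014 × 3821 = 5.3.
- All CRBSI types: 0.032 × 3821 = 122.3, of which type 1 (local infection without a positive blood culture) gives 0.031 × 3821 = 118.5.

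**Reading 2: ward means, as in Data collection**

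| Planned analysis | Can it be run on 20 ward means? |
|---|---|
| Median test | Yes, on about 10 values per arm. It compares ward averages, not patients' stays, and has little power. |
| Kaplan-Meier and log-rank test of patients' stays | No. They need each patient's own time. |
| Cox regression at patient level | No, for the same reason. |

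**Reading 3: individual stays of all ward patients**

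This fits the hypothesis and every planned analysis. It does not fit the outcome list, which names PVC-BSI cases, and Data collection does not name individual stay as an item to be collected.

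**The case against.** Several points on the other side are sound.

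- **The HLOS analysis is not impossible.** A reader might infer that no planned test can be computed. That is not so. The median test runs on ward means, and Setting declares the ward the unit of analysis, so a ward-level comparison is in keeping with the design. Only the survival analyses fail, and the article calls them supportive.
- **Individual stays are not ruled out.** The source is an electronic patient management system, patient-level information is taken at catheter removal, and the cost outcome speaks of stay for patients. This stands, but nowhere is individual stay named as an item to collect.
- **The cost analysis does not lose its input.** A reader might infer that it does. The cost outcome names its stay measure separately from PVC-BSI cases, and a ward mean can serve there.
- **These are not four separate outcomes.** Only the outcome list defines one; the other sections give a hypothesis, a data source and a method. The conflict is two populations, two data levels, and mean against median.
- **The count is soft.** Dwell is assumed. The figure of 3821 is what the primary outcome requires, not a stated total of catheters over 12 months. The article does not say that the PVC-BSI mean will be tested between arms. If every CRBSI type was meant, about 122 patients would qualify, although Definitions reserves PVC-BSI for type 3.

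None of this removes the selection on a post-randomisation event, which holds at 10 cases and at 122, or the disagreement between sections.

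**Conclusion.** The concern holds as a conflict over the population, summary and data level of HLOS. Taken literally, the listed outcome rests on about 1 to 10 patients in 3821 records at an assumed 2 to 5 days' dwell, with roughly one patient or fewer expected per arm at each time point. The count would grow in proportion if more catheters were observed. Whatever the count, a between-arm comparison in that group is not a randomised one. With ward means, the main median test is feasible but weak, and the survival analyses cannot be done.

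The documents do not support the stronger conclusion that the trial cannot examine length of stay at all. The primary outcome is not affected. The text should be corrected before the hospital extracts are requested, because their form decides which analyses remain possible.

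**What to change.** 1. **Outcome list.** Define the between-arm HLOS outcome as the individual stay, admission to discharge, of all adult inpatients on the study wards, with one stated summary and time point. Do not limit it to patients with a PVC: the secondary hypotheses expect fewer unnecessary PVCs, so having one is itself affected by the intervention. Report stays of PVC-BSI patients descriptively, without a test.
2. **Data collection.** Request admission and discharge dates per patient from the same electronic system, in place of the ward mean.
3. **Data analysis.** Make the HLOS comparison allow for ward clustering, for example by a cluster-robust or a ward-level analysis. Patient-level stays analysed by ordinary median and log-rank tests would ignore it.
4. **Fallback.** If only ward means can be obtained, compare them at ward level and drop the survival analyses.

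The cost is a change of wording and a patient-level rather than an aggregated extract, with no additional patients to recruit. Whether each hospital can supply that extract has to be confirmed, since the article describes requesting statistics reports. Including patients without a PVC will dilute any effect on stay; that is the price of comparing the wards as randomised.

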
### Sample size

Calculations are based on a previous observational pilot conducted in Manacor Hospital, which reported a global rate of 44.1% PVC-associated adverse events (16% phlebitis, 6.8% obstruction, 18.1% extravasation, and 3.2% CRBSIs rates of which 3.1% were CRBSIs type 1, 0.14% CRBSIs type 2, and none CRBSIs type 3). Similar studies have a potential for improvement between 7 and 19% in adverse event rates, such as phlebitis, infiltration, and obstruction, yet there is no statistical significance or potential for improvement in CRBSI rates [32, 33]. The initial assumption is for the intervention to decrease the rate of adverse events associated with PVC in the intervention group at 6 months post-intervention by 15%. For such target result, the sample size required would be 1920 nursing records, accepting an alpha risk of 0.05, a beta risk of 0.2 in a two-sided test, and 10% missing data. For the calculation of sample size, the smallest detectable difference with adequate power and statistical significance has been considered. The sample size has been corrected to account for within-intra cluster correlation coefficient of 0.01 to allow for a design effect of 1.99. The final sample size will therefore be of 3821 nursing records, assuming an average cluster size of 200 nursing records.

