### Primary outcome measures: effect evaluation

The primary outcome will be the incidence of adverse events associated with the use of PVCs in adult inpatients. This incidence will be determined from evaluation of hospital records at 3, 6, 9, and 12 months.

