### Intervention group

The intervention will last 12 months and will be based on a theoretical model on effective knowledge mobilization, integrating a multimodal strategy related to peripheral catheters clinical practice improvement which includes the following (Fig. 1): (1) implementation of recommendations trough up-to-date protocols and posters related to hand hygiene and aseptic measures, insertion, maintenance and removal of PVC [34]; (2) use of e-learning technologies [35–37]; (3) feedback on the results and messages addressed to healthcare professionals to facilitate adherence to recommendations [38]; (4) face-to-face training sessions [39]. Masterclass related to PVC insertion, maintenance, and removal will consist of information shared about recommendation of CPGs adapted according to the needs detected by means of the questionnaire on the effectiveness of the healthcare practice; (5) leaflets with information for patients and family/careers about peripheral catheters, in appropriate language [40]; and (6) support by internal facilitators, which will be key members of staff in the organizations, to adopt best evidence based on the PARIHS theoretical model [26, 41, 42].

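### The sample size is built for one comparison at six months post-intervention, but the primary outcome is read at four times and no contrast is designated to decide the hypothesis

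*Protocol article*

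**What the plan says.** - **Sample size.** The target is that the intervention will "decrease the rate of adverse events associated with PVC in the intervention group at 6 months post-intervention by 15" per cent. The starting point is a pilot that "reported a global rate of 44.1% PVC-associated adverse events". The error settings are given as "accepting an alpha risk of 0.05, a beta risk of 0.2 in a two-sided test, and 10% missing data", and on that basis "the sample size required would be 1920 nursing records". Multiplying by a stated design effect of 1.99 gives 3821.
- **Primary outcome measures: effect evaluation.** "This incidence will be determined from evaluation of hospital records at 3, 6, 9, and 12 months". None of the four times is marked as the main one.
- **Intervention group.** "The intervention will last 12 months".
- **Data collection.** The phases are listed as "baseline (2 months), intervention and evaluation (12 months"). The text names no later follow-up. The timeline is in Fig. 2, which was not available for this review.
- **Primary hypothesis.** One hypothesis is stated: a lower incidence of adverse events. No time is attached.
- **Effect evaluation and process evaluation.** Rate outcomes are to be compared by generalized estimating equations, with no time term or time point given. The Cochran-Mantel-Haenszel test is also listed for proportions. There is one general threshold: a p "value of < 0.05 will be considered statistically significant".

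**The concern.** The time at which the trial is powered and the times at which the primary outcome is read do not match, and neither section says which comparison decides the result. The only time point that the protocol ties to an effect is in the sample-size sentence, and that sentence does not fit cleanly into the schedule.

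Two things are at stake. First, with four assessments and no designated contrast, the decisive time could be chosen after the data are seen, or several could be tested, and the 5% error rate would then not hold. Second, the 80% power belongs to one comparison that uses all 3821 records. If those records are collected across four assessments and only one is decisive, that comparison has much less power than stated. A reader cannot tell from the article which situation applies.

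**Working it through.** **Step 1. What the stated sample size buys.** Inputs from Sample size: control rate 0.441, a 15% reduction, two-sided alpha 0.05, power 0.80, 10% missing. Read as relative, the reduction gives 0.441 × 0.85 = 0.37485, a difference of 0.06615.

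- Variance sum: 0.441 × 0.559 + 0.37485 × 0.62515 = 0.4809.
- Per arm: (1.960 + 0.842)² × 0.4809 / 0.06615² ≈ 863. With the pooled variance under the null it is 866.
- Total after 10% missing: 2 × 863 / 0.9 = 1918, or 2 × 866 / 0.9 ≈ 1925. Stated: 1920.
- 1920 × 1.99 = 3820.8. Stated: 3821.

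An absolute 15-point reduction would need only 358 records, so the relative reading is the one used. The calculation contains one comparison at 0.05 and no allowance for several.

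**Step 2. Can the powered time be placed in the schedule?**

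- *Six months after the intervention ends.* This is about month 18 from the start of a 12-month intervention. The text lists no assessment then. In favour of this reading, the secondary-outcome section attaches the post-intervention label to month 12 when it describes costs.
- *Six months after the intervention starts.* This is the 6-month assessment, which exists, but the primary-outcome section gives it no priority over months 3, 9 and 12.

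On neither reading does the text link the powered comparison to a designated primary analysis.

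**Step 3. Error rate if all four were tested and any one counted (a scheme the protocol does not state).**

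- Independent tests: 1 − 0.95⁴ = 0.185.
- Equally correlated test statistics, by simulation: about 0.156 at correlation 0.5 and 0.13 at correlation 0.7. Over assumed correlations of 0.3 to 0.9 the range is about 0.17 to 0.09.

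The correlations are assumptions, because the documents give none.

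**Step 4. Power at month 6 if the records were split evenly over four assessments (an assumption).**

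- Analysable records at month 6: 3821 / 4 × 0.9 ≈ 860, or 43 in each of 20 wards.
- Design effect with the stated intracluster correlation of 0.01: 1 + (43 − 1) × 0.01 = 1.42.
- Effective number per arm: 430 / 1.42 ≈ 303.
- Standard error: √(0.4809 / 303) ≈ 0.0398, so z = 0.06615 / 0.0398 ≈ 1.66.
- Power: Φ(1.66 − 1.96) ≈ 0.38. With a t reference on 18 degrees of freedom it is about 0.35.

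**Step 5. How much of the shortfall comes from the split.** The stated 1.99 is not the design effect for 200 records per ward at 0.01, which is 1 + 199 × 0.01 = 2.99. Using all 3821 records in one comparison:

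| Records per ward | Design effect | Effective n per arm | Power |
|---|---|---|---|
| as stated | 1.99 | 864 | 0.80 |
| 172 (analysable) | 2.71 | 635 | 0.67 |
| 191 (sampled) | 2.90 | 593 | 0.64 |

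The effective numbers are 3821 × 0.9 / 2 = 1719 divided by the design effect. On the analysable-record basis, correcting the design effect takes power from 80% to 67%, and the even split takes it from 67% to 38%.

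**The case against.** A reader might infer that the protocol plans four separate tests of the primary outcome, each at 0.05, and so has a false-positive rate of up to 18.5%. The text does not say that. The four times are when incidence is determined, the 0.05 threshold is stated once as a general rule, there is a single primary hypothesis, and the estimating-equation model could take all assessments at once. The error inflation is a risk left open, not a stated plan.

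A reader might also infer that the powered time does not exist in the schedule. That holds only if the phrase counts from the end of the intervention. The wording is ambiguous, the list of phases can be parsed in more than one way, and the timeline figure was not available, so this reading cannot be asserted as fact.

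Nor does the protocol say that the 3821 records are divided over four assessments. They are derived for the six-month target, so all could be meant for that one comparison. The 38% is therefore conditional, and part of its distance from 80% belongs to the design effect.

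Finally, a multiplicity rule and the handling of repeated assessments are commonly left to an analysis plan, and their absence from a condensed article is no fault. This argument does not dispose of the point. The article does fix a time for the powered effect, and that time does not agree clearly with its own outcome definition and schedule. That is a mismatch within the text.

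**Conclusion.** The point holds in a limited form. The sample size supports exactly one two-sided comparison at 0.05, at a time that is either unscheduled in the text or one of four unranked assessments, and no section designates the contrast that decides the primary hypothesis. That rests only on the wording and on the reproduced 1920 and 3821.

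The consequences depend on choices that the article leaves open. Family-wise error would be 18.5% for four independent tests, and about 13% to 16% at assumed correlations of 0.7 to 0.5, only if any one significant result counted as success. Month-6 power would be about 38% only if records were spread evenly. If one contrast used all 3821 records, multiplicity would need no extra records, but power would be about 64% to 67% at an intracluster correlation of 0.01, not 80%.

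**What to change.** Reconcile the Sample size, Primary outcome and Data collection sections by naming one primary contrast before any outcome data are seen.

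One workable choice is incidence over the 12-month evaluation phase, pooling all sampled records, tested once at two-sided 0.05 in a model that accounts for ward clustering and includes assessment period as a factor. The 3-, 6-, 9- and 12-month contrasts then become secondary, and the time phrase in the sample-size sentence is replaced by this contrast. Designating one existing assessment would also resolve the mismatch, provided the protocol states how many of the 3821 records come from that assessment.

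The change is mainly one of wording. Pooling does alter the target: it becomes an average over the year that includes the roll-out months, which may dilute the effect by an amount that the documents do not allow one to calculate. Whichever contrast is chosen, its power should be restated with the design effect recomputed. For the pooled contrast that is about 64% to 67% with 3821 records, so naming the contrast does not by itself restore 80%.

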### Setting

The study will be conducted in five public hospitals with diverse characteristics within the Spanish National Health System, including one reference hospital and four acute care hospitals. Twenty wards will be selected and randomly allocated to either the intervention or control groups. The intervention will be delivered at ward level, and therefore, the ward will be considered the unit of analysis. Emergency, critical care, pediatric, maternity, peri-operative, operative rooms, and psychiatric areas will be excluded from the analysis, due to the fact that peripheral catheters are routinely maintained inserted for less than 24 h. Bias-compensating measures will be incorporated to homogenize nursing practice through face-to-face training in excluded wards.

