### Randomization

Wards will be randomly allocated to the intervention or control arm using software, in blocks 1:1 with stratification by setting (medical or surgical) and hospital (to ensure homogeneity of both groups).

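### The stated ICC (0.01), design effect (1.99) and cluster size (200) cannot all hold; if ICC 0.01 and 20 wards stand, 3821 records give about 67% power, not 80%

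*Protocol article*

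**What the plan says.** All the figures but two are in the Sample size section of the protocol article.

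- **Control rate:** the pilot "reported a global rate of 44.1% PVC-associated adverse events".
- **Effect:** the intervention is assumed to "decrease the rate of adverse events associated with PVC in the intervention group at 6 months post-intervention by 15" per cent. The text does not say whether this is relative or absolute.
- **Error rates and missing data:** "accepting an alpha risk of 0.05, a beta risk of 0.2 in a two-sided test, and 10% missing data".
- **Size before clustering:** "the sample size required would be 1920 nursing records".
- **Clustering:** "within-intra cluster correlation coefficient of 0.01 to allow for a design effect of 1.99".
- **Final size:** "The final sample size will therefore be of 3821 nursing records, assuming an average cluster size of 200 nursing records".

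The Setting section fixes the number of clusters: "Twenty wards will be selected and randomly allocated to either the intervention or control groups". The Randomization section gives the allocation as "in blocks 1:1 with stratification by setting (medical or surgical) and hospital".

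**The concern.** The usual design effect for clusters of equal size is 1 + (m − 1) × ICC, where m is the number of records per cluster. With an ICC of 0.01, the printed design effect matches clusters half the size that the same paragraph assumes. The mismatch matters because the final size is the unclustered size multiplied by that design effect.

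The power of the primary comparison is at stake. If the printed ICC and ward layout are right, the chance of missing a true effect of the planned size is about one in three, not one in five. A null result would then be read as coming from a trial with 80% power when the plan's own inputs do not support that.

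**Working it through.** **1. Reproduce the plan's figures.** Control rate 0.441; a 15% relative reduction gives 0.441 × 0.85 = 0.37485, a difference of 0.06615. The sum of the two binomial variances is 0.441 × 0.559 + 0.37485 × 0.62515 = 0.2465 + 0.2343 = 0.4809.

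n per arm = (1.96 + 0.8416)² × 0.4809 / 0.06615² = 862.5, so 1725 in total. Dividing by 0.9 for missing data gives 1917. The pooled-variance formula gives 1925. Both agree closely with the stated 1920. An absolute drop of 15 points would need only about 358 records, so the relative reading is the one that fits.

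1920 × 1.99 = 3820.8, the stated 3821.

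**2. Check the design effect at ICC 0.01.**

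- m = 100: 1 + 99 × 0.01 = 1.99
- m = 200: 1 + 199 × 0.01 = 2.99
- m = 3821/20 = 191: 1 + 190 × 0.01 = 2.90

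The 20 wards agree with clusters of about 200. Clusters of 100 would mean 3821/100, or about 38 wards. To get 1.99 at m = 200, the ICC would have to be 0.99/199 = 0.00497.

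**3. Power at each design effect (DE).** Power = Φ(0.06615 / √(0.4809 / n) − 1.96), where n = N / DE / 2 is the effective number per arm. With 10% missing, N = 0.9 × 3821 = 3439.

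| Records analysed | Records per ward used in DE | DE | Effective total | Power |
|---|---|---|---|---|
| 3439 | 100 (implied by 1.99) | 1.99 | 1728 | 80.1% |
| 3439 | 200 | 2.99 | 1150 | 62.8% |
| 3439 | 191 | 2.90 | 1186 | 64.2% |
| 3439 | 172 (3439/20) | 2.71 | 1269 | 67.1% |
| 3821 | 200 | 2.99 | 1278 | 67.4% |
| 3821 | 191 | 2.90 | 1317 | 68.7% |

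The first row recovers the stated power, so the method matches the plan's and only the design effect differs. The fourth row is the one consistent with both 20 wards and 10% missing: 3439/20 = 172 analysable records per ward, and 1 + 171 × 0.01 = 2.71.

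**4. Detectable effect.** With 3439 records, solving the same formula for 80% power gives a relative reduction of 17.4% (7.7 points) at DE 2.71 and 18.3% (8.1 points) at DE 2.99.

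**5. If the ICC was meant to be 0.005.** At m = 200 the design effect is 1 + 199 × 0.005 = 1.995, and 3439 records give 80.0% power. The product 1920 × 1.995 = 3830 is close to 3821 but does not equal it.

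**The case against.** The strongest reply is that three inputs conflict and the article does not say which is wrong. A reader might infer that the design effect is certainly the error and that the trial is therefore certainly underpowered. The text does not support that much. An ICC of 0.005, rounded to 0.01 in print, would resolve the conflict and leave about 80% power. Against this, the printed ICC is 0.01, and only 1.99 exactly, which is the value for ICC 0.01 and m = 100, reproduces 3821. The objection therefore stands as a condition on the power figure. It does not remove the contradiction.

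A reader might also infer that power is 63%, or even 58%. The 63% removes 10% of the records but still uses 200 per cluster, which is 3439/200, or about 17 wards, not 20. It is the lower end of a range, not the best figure for the stated layout. The 58% adds a t reference on 18 degrees of freedom (20 wards less 2). That is a separate small-sample choice, commonly left to an analysis plan, and it would lower power to 75.6% even at a design effect of 1.99.

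Finally, the simple two-proportion calculation does not settle the power of the eventual analysis. Outcomes are evaluated at 3, 6, 9 and 12 months, the article does not say whether 3821 covers one time point or all, stratified allocation could recover some precision, and unequal ward sizes would lose some. None of this can be quantified from the document. The plan's own calculation claims none of it, so it does not justify the 1.99.

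**Conclusion.** The point holds. The ICC, design effect and cluster size printed in the Sample size section are mutually incompatible, no other section reconciles them, and the incompatible multiplier sets the final size. If ICC 0.01 and 20 wards stand, 3821 records give about 67% power with 10% missing, with a range of 63% to 69% across treatments of the missing data, against the stated 80%.

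The figure assumes equal ward sizes, a 15% relative reduction from 44.1%, a two-sided 5% normal-theory test, and no gain from stratification. It depends on 0.01 being the intended ICC, which the article prints but which may itself be the misstated input.

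**What to change.** 1. Confirm which of the three inputs is misstated. If the ICC was meant to be 0.005, print that value with a design effect of 1.995; the power then remains about 80%.
2. If ICC 0.01 stands, correct the design effect to 2.99 for 200 records per ward, or 2.90 for 191. Then either restate the power for 3821 records in 20 wards as about 67% (range 63% to 69%), or restate the relative reduction detectable at 80% power as about 17% to 18%.
3. Label the 15% as a relative reduction.
4. If a t reference on 18 degrees of freedom is planned, note its effect separately (about 62% at a design effect of 2.71) and do not merge it into the corrected figure.

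The cost is a few restated figures and, if ICC 0.01 stands, a less favourable stated power. No extra enrolment is needed.
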